#### 3.6.2. Secondary Outcome Measures

Secondary outcome measures will include: glycemic control, medication use, demographic factors, physical factors, psychosocial factors, and exposure to health provider support. 

##### Glycemic Control

HbA1c reflects average plasma glucose over the previous six to eight-week period [48,49]. In Australia, it is best practice for GPs to conduct HbA1c testing on people with T2D every 3 months [8]. The test is subsidized by Medicare, the Australian Government’s universal health scheme, up to four times in a 12-month period [50]. The GP on the research team will retrospectively obtain participants’ HbA1c results over the 12-month study period from the relevant pathology laboratory. Other blood results collected will include; fasting blood glucose, high-density lipoprotein cholesterol, low-density lipoprotein cholesterol, and C-reactive protein. 

##### Medication Use

Information on all medication use (name of medication and dosage) will be collected, including over-the-counter, and complementary medicines.

##### Demographic Factors 

Demographic factors collected at baseline including; age, gender, highest education level, living arrangement, self-selected social class, household income, ability to manage on income, and smoking status. Response options will be dichotomous (e.g., gender), continuous (e.g., age) or categorical (e.g., highest educational level), consistent with categories used in the national consensus by the ABS.

Age and Gender

Participants’ age at last birthday and gender will be collected. Sex response options will include three categories in line with the ABS 2016 Census; male, female and other [51]. 

Highest Education Level 

Collecting data on highest educational level helps generate a single measure of an individual’s overall educational attainment, whether it be a school or non-school qualification [51]. Participants will be asked to report their highest education level from eight categories in line with the ABS 2016 Census; postgraduate degree, graduate diploma and graduate certificate, bachelor degree, advanced diploma, diploma, certificate, year 12, or year 11 and below [51]. 

Living Arrangement 

Data on participants’ current living arrangement will be collected. In line with the ALSWH, response options will include; no one, partner/spouse, own children, someone else’s children, parents, or other adults [29]. 

Self-Selected Social Class 

Requesting information on self-selected social class allows class designation to be meaningful to participants and is more likely to reflect their actual class identity [52]. Participants will be asked to self-select their social class from one of four response options in line with the ALWHS; ‘upper class’, ‘middle class’, ‘working class’, or ‘don’t know’ [52]. 

Household Income and Ability to Manage on Income 

Gross income refers to the sum of income received from all sources before any deductions (income tax, the Medicare Levy or salary sacrificed amounts) are taken out [51]. Participants will be asked to report their average yearly gross household income from six response options in line with the ALSWH; less than $20,000, $20,001–$30,000, $30,001–$50,000, $50,001–$100,000, more than $100,000 or ‘don’t know/would rather not say’. Details on participants’ ability to manage on their current income will also be collected. Seven response options in line with the ALSWH will include; ‘impossible’, ‘difficult’, ‘always difficult’, ‘sometimes difficult’, ‘not too bad’, ‘easy’, or ‘not sure’ [53].

Smoking Status 

Participants will be asked to report their smoking status. Wording of the question has been developed to correspond with the ABS 2016 Census and response categories will include ‘yes’ or ‘no’ [51].

##### Physical Factors

Self-reported anthropometric data is valid and recommended for monitoring prevalence of obesity, particularly for large-scale studies because of its simplicity and low cost [54,55,56]. Physical factors will include; self-reported waist circumference, weight, and height. All response options will be continuous. 

Waist Circumference 

Waist circumference is a better indicator of central obesity than BMI or waist-to-hip ratio and is more strongly correlated with intra-abdominal fat content and cardiovascular risk factors [57]. Participants will be asked to self-report their waist circumference to the nearest centimeter. Participants will be asked to report results of two measures at each round of data collection, which will be averaged during data analysis. Measuring instructions adapted from the ALSWH will be provided to participants in the postal envelope [58]. Instructions will request participants to measure mid-central adiposity using the tape to measure at the level of the mid-point between the lower costal border and the iliac crest [58].

Weight

Weight will be self-reported at each data collection point to the nearest decimal point. If the participant can only report the amount in stones and pounds, a conversion factor of 2.203 will be used to convert pounds into kilograms in line with the ALSWH [52]. Participants will be asked to describe where and how their weight was measured to assess the accuracy of the information.

Height

Height will be self-reported to the nearest centimeter at baseline only. If the participant can only report the information in feet or inches, a factor of 2.54 will be used to convert inches to centimeters in line with the ALSWH [52].

BMI

BMI provides the most useful population-level measure of obesity [58,59]. Participants’ BMI will be calculated after each round of data collection using the standard equation (weight (kg)/height (m)^2^) [58]. Participants will be grouped into BMI categories for analysis according to the World Health Organization guidelines; underweight (<18.50 kg/m^2^), normal weight (18.50–24.99 kg/m^2^), overweight (≥25.00 kg/m^2^) and obese (≥30.00 kg/m^2^) [59].

Physical Activity 

Regular physical activity is a key feature of international T2D management guidelines [9,60]. This is because it has been shown to improve glycemic control (regardless of whether weight loss has occurred), lipid levels, and blood pressure in people with T2D [61,62,63]. Participants’ physical activity levels will be measured through the IPAQ-SF which is one of the most widely used physical activity assessment questionnaires and has been shown to be a valid measure of obtaining internationally comparable physical activity data [64,65]. It measures self-reported physical activity in the previous seven days and includes seven items that collect information on walking time, moderate and vigorous physical activity time and sitting time [66]. Data obtained in the IPAQ-SF will be used to estimate total metabolic equivalent (MET)-minutes per week for each participant [67].

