#### 3.6.1. Primary Outcome Measure: Change in Diet Quality (measured by DASH score)

Diet quality can be measured by a variety of purpose developed tools [31]. These are constructed by assigning higher scores within sub-scales based on more frequent or higher intakes of foods, nutrients or both [31]. Dietary Approaches to Stop Hypertension (DASH) is a dietary pattern high in whole-grains, fruits, and vegetables; moderate in low-fat dairy; and low in red and processed meats, added sugars, and sodium [32]. While originally developed to assist people in the prevention and management of hypertension, DASH is now recommended for the dietary management of T2D [18,33]. Adherence to DASH positively impacts on glycemic control, weight, and hypertension, which are key indicators of risk for diabetes-related complications [5,18,32]. A randomized controlled trial (RCT) conducted in adults with T2D showed that adherence to DASH improved glycated hemoglobin (HbA1c) (−1.2%), fasting blood glucose (−0.92 mmol/L), weight (−3 kg) and waist circumference (−4.8 cm) over 8 weeks when compared with a control diet [34,35]. Those following the DASH dietary pattern, also had a greater reduction in LDL cholesterol (difference from the control diet, −7.7 ± 3.3%).

A systematic review and meta-analysis of 20 RCTs found DASH significantly reduced systolic (−5·2 mmHg) and diastolic blood pressure (−2·6 mmHg) in adults with and without diabetes [36]. Another systematic review and meta-analysis of 13 RCTs revealed that adults without T2D who adhered to DASH achieved greater weight loss (−1.42 kg), reduced Body Mass Index (BMI) (−0.42 kg/m^2^) and decreased waist circumference (−1.05 cm) compared with controls [37]. Considering the recognized impact on glycemic control, weight and hypertension, DASH was chosen as the dietary pattern used to assess diet quality in the present study. Participant DASH scores will be calculated using the DASH diet-quality tool which has been shown to have the highest correlation with health outcomes related to T2D compared to other tools that measure diet quality [38,39].

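### BMI is grouped into four WHO bands for analysis although it is computed as a continuous value at every round, and overweight as written overlaps obese

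*Protocol article*

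**What the plan says.** In the protocol article, section 3.6.2 (Physical Factors), waist, weight and height are collected on a continuous scale: "All response options will be continuous". BMI is derived repeatedly: "Participants’ BMI will be calculated after each round of data collection using the standard equation". The next sentence fixes how it is used: "Participants will be grouped into BMI categories for analysis according to the World Health Organization guidelines". The lower two bands are "underweight (<18.50 kg/m^2^), normal weight (18.50–24.99 kg/m^2" and the upper two are "overweight (≥25.00 kg/m^2^) and obese (≥30.00 kg/m^2". Normal weight is closed at both ends; overweight is open at the top.

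The same section keeps two other measures of body size in continuous form. For weight: "Weight will be self-reported at each data collection point to the nearest decimal point". For waist: "Participants will be asked to report results of two measures at each round of data collection, which will be averaged during data analysis".

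Section 3.8 lists physical measures among the explanatory variables for 12-month DASH score. It does not say which ones enter or in what form. Aim (ii) in the Introduction is to find demographic, physical and psychosocial predictors of improvement in diet quality and glycemic control.

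**The concern.** There are two separate faults.

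The first is definitional. A participant with a BMI of 32 satisfies both the overweight and the obese criterion, so the groups are not mutually exclusive as written.

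The second is an analysis choice. BMI is available as a continuous number at five time points, and the only use the article states is in four bands. Within a band all values are treated as equal, and the top band has no limit. If the bands are what enters the model, a real linear association between BMI and the outcome is estimated less precisely than the data allow, and within-person change registers only when someone crosses a cut-point. Precision is likely to be scarce. Section 3.3 reports 22 recruits from 1000 invitations in the feasibility study, of whom 17 completed baseline and six had left by 3 months. Section 3.8 sets no initial sample size.

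**Working it through.** The article gives no figure for this point to reproduce, so the check quantifies what banding would cost.

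**Inputs from the article.** Cut-points 18.5, 25 and 30 (3.6.2). Changes cited in 3.6.1: "weight (−3 kg) and waist circumference (−4.8 cm) over 8 weeks" from a trial in adults with T2D; −1.42 kg and −0.42 kg/m² from a meta-analysis in adults without T2D.

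**Assumptions not in the article.** BMI normal, truncated at 15, mean 28–34 and SD 5–7; height 1.60–1.80 m. Overweight is read as 25.00–29.99. Simulation used 1,000,000 draws per scenario.

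**1. Overlap.** The share meeting both definitions is the share with BMI ≥30: 34% (mean 28, SD 5) to 79% (mean 34, SD 5). That the bands overlap needs no assumption; only the share does.

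**2. Variance kept by the bands.** Variance kept = between-band variance ÷ total variance. For a linear effect, the approximate sample-size multiplier is its inverse.

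| Mean BMI | SD 5 | SD 6 | SD 7 |
|---|---|---|---|
| 28 | 0.834 | 0.831 | 0.822 |
| 30 | 0.771 | 0.775 | 0.771 |
| 32 | 0.668 | 0.692 | 0.700 |
| 34 | 0.533 | 0.583 | 0.613 |

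The loss runs from 1 − 0.834 = 17% to 1 − 0.533 = 47%, and is 31% at mean 32, SD 6. The multipliers are 1/0.834 = 1.20, 1/0.533 = 1.88 and 1/0.692 = 1.45.

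Hand check at mean 32, SD 6, without truncation. The standardised cut-points are −2.25, −1.167 and −0.333, with normal densities 0.0317, 0.2020 and 0.3774 and band probabilities 0.0122, 0.1095, 0.2478 and 0.6306. The variance kept is the sum over bands of (difference in density at the band's edges)² ÷ band probability: 0.082 + 0.265 + 0.124 + 0.226 = 0.70. This agrees with the simulated 0.69.

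**3. Sensitivity to weight change.** BMI change = kg ÷ height². For 3 kg this is 3/1.80² = 0.93 to 3/1.60² = 1.17 kg/m². If everyone lost the same amount, the share changing band would be:

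| Loss | Share changing band |
|---|---|
| 3 kg | 8–19% |
| 1.42 kg | 3–9% |
| 0.42 kg/m² | 3–7% |

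For 3 kg, 81–92% would therefore show no change in band.

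Hand check for 3 kg at 1.70 m (1.04 kg/m²), mean 32, SD 6. Those who cross lie within 1.04 above a cut-point. Density at mid-interval × 1.04 gives 0.067 (above 30) + 0.039 (above 25) + 0.007 (above 18.5) = 0.11, matching the simulated 0.112.

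**4. Band width.** The overweight band spans 5 kg/m², or 5 × 1.60² = 12.8 kg to 5 × 1.80² = 16.2 kg. In the obese band, a fall from BMI 40 to 30 at 1.70 m is 10 × 1.70² = 28.9 kg with no change of band.

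**The case against.** The strongest reply is that the banded variable is not the study's only record of body size. Weight is taken at every round to a decimal and waist as the mean of two readings, both continuous. Height is recorded at baseline only, so a participant's BMI change is weight change divided by a constant. A reader might infer from the banding that most weight change is hidden from the study; the article does not support that. The insensitivity belongs to the BMI band variable alone.

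A reader might also infer residual confounding by adiposity in the diet–HbA1c association of aim (iii). That would require BMI band to be the sole adiposity adjustment, which the article nowhere says. Section 3.8 speaks of physical measures in the plural, and 3.6.2 ranks waist above BMI as a marker of central fat.

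It can further be said that grouping for analysis may mean descriptive or subgroup use, and that a covariate's functional form is often left to an analysis plan, which is not shown here. This stands in part: the text does not say that the bands replace continuous BMI in the regression, so the loss is conditional. But the article does make a positive statement about analysis and mentions no continuous use of BMI, so the statement can fairly be corrected where it stands.

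The overlap has one sensible reading, overweight as 25.00–29.99. It discards no information and is independent of the loss from banding.

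Finally, the 3 kg figure is a between-group difference in an 8-week trial, not a forecast for this cohort. It is used here only as a yardstick the article itself supplies.

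**Conclusion.** The point holds as a minor one. As written, the overweight and obese groups overlap; this is certain but only a matter of wording. If the bands enter the regressions as the physical predictor for aim (ii), they lose about 17–47% of BMI's variance for a linear effect, equivalent to needing roughly 1.20–1.88 times as many participants for the same precision on that term. The band variable would fail to register a 3 kg loss in about 81–92% of participants.

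These sizes rest on an assumed normal BMI distribution and assumed heights. Banding loses information throughout the range examined, but the amount depends on the cohort's actual mean and spread. They also refer to a linear effect of BMI taken alone: the practical cost is smaller if continuous weight or waist is in the same model. BMI is one explanatory variable among many and is not the primary outcome.

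**What to change.** In 3.6.2, state that BMI enters the regression models as a continuous term (linear, or a spline if the relation is curved), and that the WHO bands are for descriptive tables only. Write overweight as 25.00–29.99. Because height is fixed at baseline, BMI and weight carry the same within-person change, so it would help to state which of the two is the time-varying term.

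The cost is a sentence or two of text. No new data, procedure or clinical decision is involved. A spline uses a few extra parameters, so with a small sample the linear term is the natural default. The WHO bands remain available for comparison with other surveys.

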##### Psychosocial Factors

Healthful Eating Beliefs 

Healthy eating beliefs will be investigated at each of the five data collection points to better understand their beliefs, attitudes and intentions towards making positive dietary behaviors and how these impact on diet quality change over time. Participants’ healthy eating beliefs will be assessed through the Healthful Eating Beliefs Scale. This scale is based on the TPB [68]. Standardized questions have been selected from previous Healthful Eating Beliefs Scales to suit the current study. Table 4 provides an outline of the rationale for investigation behind the questions and modes of responses. Participant scores will be generated for each of the seven subscales of the Healthful Eating Beliefs Scale by calculating the mean of the 5-point Likert scale items, with higher scores representing more positive beliefs, attitudes, and intentions towards improving dietary behaviors.

Mental Health

Mental health data will be collected at baseline, 6 and 12 months using the internationally validated K10 questionnaire [69]. This 10-item questionnaire yields a global measure of distress based on questions about anxiety and depressive symptoms experienced in the most recent four-week period [70]. It is scored using a five-level response scale based on the frequency of symptoms reported for each question. One is the minimum score for each item (none of the time) and five is the maximum score (all of the time). The maximum score is 50 indicating severe distress, the minimum score is 10 indicating no distress [70]. 

##### Exposure to GP and Allied Healthcare Support

Interactions with health professionals may help facilitate positive changes in dietary behaviors [73]. At each data collection point, participants will be asked about their concurrent and previous exposure to healthcare provider support (e.g., dietitian, diabetes educator). Participants will also be asked to report how useful they found the advice on a 5-point Likert scale (1 being ‘not at all useful’, 2 being ’slightly useful’, 3 being ‘neutral’, 4 being ‘somewhat useful’ and 5 being ‘extremely useful’). Question wording has been modified from previously conducted qualitative research that explored the experiences of dietary change in people with T2D [13].

### 3.7. Participant Confidentiality 

All study related information will be de-identified and stored securely online with password-protected access systems. Daily back-ups of all electronic data will occur to minimize any risk of lost data. Only members of the research team who need to contact study patients, enter data or perform data quality control will have access to participant information.

### 3.8. Statistical Modeling and Sample Size 

The longitudinal aspect of diet quality change will be analyzed using regression models [74]. Diet quality at 12 months (measured by the DASH score) will be the primary outcome, with glycemic control, interim diet changes (primarily at 3 months), medication use, demographic measures, physical measures, psychosocial measures, and exposure to healthcare provider support as the explanatory variables. This model will determine the relative importance of diet quality change both immediately after diagnosis and in the medium term with regards to a 12-month outcome towards sustained healthy eating. 

Sample size calculations, such as those provided in Diggle et al. [74] are not readily computed for complex regression models and assessment using simulation studies would be more appropriate [75]. However, due to the relatively small participation rate in the feasibility study (22 participants/1000 invited) credible model parameters are currently unable to be formulated, and the effect differences over time cannot be reliably inferred. Additionally, current research of diet quality change post diabetes is lacking [15], therefore effects cannot be competently elicited. As a result, rather than determining an initial sample size for the study, a Bayesian updating procedure will be used to collect data. In this manner, sample size will be calculated during the early stages of data collection to yield an idea of how many samples should be collected. Additionally, using a Bayesian framework, the parameter estimates of the mixed model will be sequentially updated as batches of data are obtained, a process known as Bayesian learning [76,77]. 

## 4. Discussion

The study described in this paper, the 3D Longitudinal Study, will be the first to observe changes in diet quality in people with T2D after diagnosis and the factors (demographic, physical, and psychosocial) that influence those changes. Longitudinal studies help highlight differences or changes in the values of one or more variables between different time periods, describe participants’ intra-individual and inter-individual changes over time and monitor the magnitude and patterns of those changes [78]. This is important for the proposed research because it is necessary to understand the extent to which people change their diet after a T2D diagnosis and why some people are able to sustain these changes over time and others are not. Understanding this will help to develop targeted strategies and facilitate enhanced dietary behavior support important to assist all people with T2D to have long-term success in improving their diet quality and help reduce the risk of complications. The results of this study will significantly add to the body of literature on the diet quality changes of people diagnosed with T2D, which is an under-researched area.

Limitations of the 3D Longitudinal Study are acknowledged. Recruitment through the NDSS is the most suitable way to access a large number of potential participants with T2D, however selection bias cannot be excluded as registration is voluntary, so participants may have greater diabetes self-management motivation. Self-reported dietary intake data and physical measurements may introduce misreporting bias and social desirability responses. Measurement errors associated with dietary assessment methods are also acknowledged. However, use of the ASA-24 h dietary recall (Australian version) which is a validated tool specifically designed for the Australian population, reduces risk of bias [43]. A feasibility study for this project has already determined that its recruitment capability, data collection and analysis procedures are achievable and appropriate. 

## Figures and Tables

**Figure 1 nutrients-11-00158-f001:**
[figure not shown]
Recruitment and contact process for the 3D Longitudinal Study.

**Table 1 nutrients-11-00158-t001:** Inclusion and exclusion criteria for the 3D Longitudinal Study.

Inclusion Criteria	Exclusion Criteria
Adults aged >18 years	Individuals aged <18 years.
Diagnosed with T2D <6 months prior to recruitment contact	Diagnosed with LADA, T1D, gestational diabetes or pre-diabetes
Registered with the Australian NDSS and indicated their willingness to be contacted for research purposes.	Individuals who have been placed on a special diet due to a co-morbidity (e.g., renal disease)
Able to communicate in English	

LADA, Latent Autoimmune Diabetes in Adults; NDSS, National Diabetes Service Scheme; T1D, Type 1 diabetes; T2D, Type 2 diabetes.

**Table 2 nutrients-11-00158-t002:** Overview of data collection points in the 3D Longitudinal Study.

Data Collection Methods	Time Collected				
	0 Months	3 months	6 Months	9 Months	12 Months
Diet quality	✔	✔	✔	✔	✔
Glycemic control	✔	✔	✔	✔	✔
Medication use	✔	✔	✔	✔	✔
Baseline demographic factors	✔				
Physical factors	✔	✔	✔	✔	✔
Psychosocial factors	✔	✔	✔	✔	✔
Exposure to allied healthcare support	✔	✔	✔	✔	✔

**Table 3 nutrients-11-00158-t003:** Dietary Approaches to Stop Hypertension (DASH) dietary pattern scoring criteria.

Component	Foods	Scoring Quintiles (Q) *
Fruits	All fruits and fruit juices	Q1 = 1 point Q2 = 2 points Q3 = 3 points Q4 = 4 points Q5 = 5 points
Vegetables	All vegetables except potatoes and legumes	
Nuts and legumes	Nuts and peanut butter, dried beans, peas, tofu	
Whole-grains	Brown rice, dark breads, cooked cereal, whole-grain cereal, other grains, popcorn, wheat germ, bran	
Low-fat dairy	Skim milk, yogurt, cottage cheese	
Sodium	Sum of sodium content of all foods	Q1 = 5 points Q2 = 4 points Q3 = 3 points Q4 = 2 points Q5 = 1 point
Red and processed meats	Beef, pork, lamb, deli meats, organ meats, hot dogs, bacon	
Added sugar	Foods and beverages with added sugars (i.e., sugar sweetened beverages)	

* Q1 represents low consumption and Q5 represents high consumption.

**Table 4 nutrients-11-00158-t004:** Healthful Eating Beliefs Scale rationale for investigation and modes of responses.

Category	Rationale for Investigation	Area of Enquiry	Standardized Questions and Response Options	Source
Healthful Eating Beliefs Scale	To better understand healthy eating beliefs among participants and determine if they change over time.	Behavioral intention	“I intend to eat a healthful diet each day in the next 2 months,” 5-pt Likert “I will try to eat a healthful diet each day in the next 2 months,” 5-pt Likert “I plan to eat a healthful diet each day in the next 2 months,” 5-pt Likert	[68]
		Perceived behavioral control	“I have the self-discipline to eat a healthful diet” 5-pt Likert “I have the ability to eat a healthful diet” 5-pt Likert “Me eating a healthful diet would be easy/difficult” 5-pt Likert “Whether I do or do not follow the recommendations for my diet is entirely up to me” 5-pt Likert	[71]
		Subjective norm	“People important to me think I should not/I should eat a healthful diet” 5-pt Likert “Other people expect me to follow the daily recommendations for diet” 5-pt Likert “People important to me want me to eat a healthful diet” 5-pt Likert “Other people with diabetes follow the daily recommendations for diet” 5-pt Likert	[71,72]
		Attitudes towards self-care	“Following the recommendations for my diet would be harmful/beneficial” 5-pt Likert “It would be worthless/valuable for me to follow the daily recommendations for my diet” 5-pt Likert “Following daily recommendations for diet is unnecessary/necessary” 5-pt Likert Following daily recommendations for diet is unpleasant/pleasant” 5-pt Likert	[72]
